# Effects of the traditional Chinese medicine *Yi Shen Jian Gu* granules on aromatase inhibitor-associated musculoskeletal symptoms: a study protocol for a multicenter, randomized, controlled clinical trial

**DOI:** 10.1186/1745-6215-15-171

**Published:** 2014-05-15

**Keywords:** Traditional Chinese medicine, Aromatase inhibitor-associated musculoskeletal symptoms, Breast cancer

## Abstract

**Background:**

Aromatase inhibitors (AIs) are widely used as an adjuvant endocrine treatment in postmenopausal women with early-stage breast cancer. One of the main adverse effects of AIs is musculoskeletal symptoms, which leads to a lower quality of life and poor adherence to AI treatment. To date, no effective management of aromatase inhibitor-associated musculoskeletal symptoms (AIMSS) has been developed.

**Methods/design:**

To determine whether the traditional Chinese medicine *Yi Shen Jian Gu* granules could effectively manage AIMSS we will conduct a multicenter, randomized, double-blind, placebo-controlled clinical trial. Patients experiencing musculoskeletal symptoms after taking AIs will be enrolled and treated with traditional Chinese medicine or placebo for 12 weeks. The primary outcome measures include Brief Pain Inventory-Short Form, Western Ontario and McMaster Universities Osteoarthritis Index, and Modified Score for the Assessment and Quantification of Chronic Rheumatoid Affections of the Hands, which will be obtained at baseline and at 4, 8, 12 and 24 weeks.

**Discussion:**

The results of this study will provide a new strategy to help relieve AIMSS.

**Trial registration:**

ISCTN: ISRCTN06129599 (assigned 14 August 2013).

## Background

Third-generation aromatase inhibitors (AIs; that is, anastrozole, letrozole and exemestane) have become the standard of care for the adjuvant treatment of hormone-responsive breast cancer in postmenopausal women. For many years, tamoxifen was the cornerstone of endocrine therapy
[1]. However, recent clinical trials of AIs have shown benefits over tamoxifen. The main advantages are improvement of disease-free survival, decreased rates of contralateral breast cancer and a more favorable toxicity profile, with lower rates of thromboembolic phenomena and endometrial malignancy
[2-8]. These trials reported incidences of musculoskeletal symptoms ranging from 5% to 35%. Observational studies, however, have shown that aromatase inhibitor-associated musculoskeletal symptoms (AIMSS) are more prevalent than originally reported
[9,10]. In a cross-sectional survey of 200 women receiving adjuvant AI therapy for breast cancer, 94 (47%) reported AI-associated joint pain, and 88 (44%) reported joint stiffness; nearly 13% of patients discontinued therapy because of intolerable musculoskeletal symptoms
[9]. Because the mechanisms mediating AIMSS are not clearly understood, effective management of AIMSS has not yet been developed.

Potential interventions for AIMSS usually include nonsteroidal anti-inflammatory drugs, analgesics, calcitriol agents, vitamin D, and exercise. Some patients even have to switch AIs or switch to tamoxifen because of severe musculoskeletal symptoms
[11,12]. However, it is not clear whether any of these interventions have had a dramatic effect on musculoskeletal symptoms. Therefore, due to the unsatisfactory response to current symptomatic treatments, many patients seek help from traditional Chinese medicine (TCM).

TCM, which has a unique advantage in alleviating symptoms and improving quality of life, has been widely applied in China for the treatment of cancer-related side effects, such as nausea, vomiting, fatigue, tidal fever, and pain
[13,14]. Postmenopausal women with AIMSS exhibit a specific pathological change associated with deficiency of kidney essence and depression of liver qi, according to TCM theory
[15]. Insufficient kidney essence results in failure to nourish the related body constituents and organs, including bone and joints. Liver qi depression leads to stagnation of qi movement, manifested as pain
[16]. Through prescription of *Yi Shen Jian Gu* granules (YSJG), which, according to therapeutic principle of TCM, would tonify the kidney, fortify the bone, soothe the liver, regulate qi and unblock the collateral, we noted that AIMSS could be partly relieved in clinical practice. YSJG has been commonly used in our hospital for the treatment of musculoskeletal symptoms, including bone pain, myalgia, and arthralgia, in patients with osteoporosis or arthrosis. However, useful empirical observation is insufficient. Therefore, there is a need for a well-designed clinical trial to investigate the efficacy and safety of YSJG on AIMSS. The results of this study will provide clinical evidence on the efficacy and safety of YSJG in patients with AIMSS.

## Methods/design

### Study design

This study is a multicenter, randomized, double-blind, placebo-controlled clinical trial with two parallel arms (Figure 1). The aim of the study is to evaluate whether TCM (YSJG) is effective to relieve AIMSS in patients with breast cancer. Eighty-four participants will be recruited from three centers: Beijing Hospital of Traditional Chinese Medicine affiliated with Capital Medical University, Beijing Cancer Hospital, and Guang’ Anmen Hospital affiliated with China Academy of Chinese Medical Sciences. All participants will be prescribed one of the following AIs: anastrozole (Arimidex, AstraZeneca Pharmaceutical Co., [name]; 1 mg/day), letrozole (Femara, Novartis Pharma Schweiz AG, [name], or Letrozole Tablets, Jiang Su Heng Rui Medicine Co., Ltd, [name]; 2.5 mg/day), or exemestane (Aromasin, Pfizer Inc., [name]; 25 mg/day). After a 2-week run-in period, eligible participants will be randomly assigned to the TCM group or the placebo group. Considering that the majority of postmenopausal women who are taking AI need to receive calcium and vitamin D, and in order to maintain the homogeneity between patients, we will prescribe calcium carbonate and vitamin D3 tablets for all participants (each tablet is comprised of 600 mg calcium and 125 IU vitamin D3; participants take two tablets daily for 12 weeks; Wyeth Pharmaceutical Co. Ltd, [name]). The TCM group will receive YSJG granules, and the placebo group will receive placebo granules. Both groups will have a 12-week treatment period and a 12-week follow-up period. Five visits will be scheduled for each patient in their respective centers: one visit each at weeks 0, 4, 8, 12, and 24.

**Figure 1 F1:**
[figure not shown]
**Project overview. **^1^BPI-SF: Brief Pain Inventory-Short Form (Chinese version). ^2^WOMAC 3.1 Index: Western Ontario and McMaster Universities Osteoarthritis Index (Chinese version). ^3^M-SACRAH: Modified Score for the Assessment and Quantification of Chronic Rheumatoid Affections of the Hands (Chinese version). ^4^FACT-B: the Functional Assessment of Cancer Therapy breast cancer-specific quality of life tool (Chinese version). ^5^BMD: bone mineral density. ^6^Safety assessment: blood routine test, urine routine test, feces routine test, kidney function test, liver function test, estradiol (E2), follicle-stimulating hormone, tumor markers (CEA, CA125, and CA153). AIMSS, aromatase inhibitor-associated musculoskeletal symptoms; TCM, traditional Chinese medicine; YSJG, *Yi Shen Jian Gu* granules.

### Ethical issues

The trial will be conducted in accordance with the Declaration of Helsinki and the Ethical Guidelines for Clinical Research, and the trial protocol has been approved by the Research Ethical Committee of Beijing Hospital of Traditional Chinese Medicine Affiliated with Capital Medical University (ref: 201337). This trial was registered with ISRCTN at Current Controlled Trials (ISRCTN06129599).

### Study participants

Participants will be recruited from three hospitals (Beijing Hospital of Traditional Chinese Medicine, Beijing Cancer Hospital, and Guang’ Anmen Hospital) by poster and website advertisements. Informed consent will be obtained from all participants before randomization. Eligibility and exclusion criteria are presented in Table 
1.

**Table 1 T1:** Eligibility criteria

	**Inclusion criteria**
1.	Pathologically confirmed stage I to III breast cancer with no recurrence and metastasis.
2.	Completed chemotherapy and/or radiotherapy.
3.	Currently using a third-generation aromatase inhibitor (anastrozole, letrozole, or exemestane) and self-reported ongoing musculoskeletal symptoms (arthralgia and/or stiffness and/or swelling in one or more joints, bone pain, myalgia, carpal tunnel syndrome, trigger finger), which started or worsened after initiation of aromatase inhibitor therapy and has continued for more than 1 month, and who had a baseline worst pain score over the past week on the Brief Pain Inventory-Short Form ≥3 points on a scale of 0 to 10.
4.	Eastern Cooperative Oncology Group performance status 0-2.
5.	Provided written informed consent before enrollment.
	**Exclusion criteria**
1.	Patients with endocrine and any other diseases influencing bone metabolism (for example, hyperthyroidism, hypothyroidism, diabetes, Cushing’s syndrome, chronic liver disease, nephropathy, myeloma, bone tumor, or bone metastasis).
2.	Used of agents influencing bone metabolism (for example, glucocorticoid, thyroid hormone, heparin, anticonvulsants, diuretics, or bisphosphonates), except calcium agents, within the past 3 months.
3.	Contraindications to calcium agents and vitamin D.
4.	Diagnosed with primary osteoarticular diseases.
5.	Presence of other primary tumors and severe heart, liver, kidney, and hematopoietic system diseases.
6.	Presence of pregnancy, mental illness, or cognitive handicap.

### Interventions

For the treatment group, YSJG granules are composed of 12 herbs, including *Radix rehmanniae Preparata* (ShuDiHuang), *Semen cuscutae* (TuSiZi), *Rhizoma cyperi* (XiangFu), *Rhizoma chuanxiong* (ChuanXiong), *Rhizoma corydalis* (YanHuSuo), *Caulis trachelospermi* (LuoShiTeng), and so forth. Because the formula for YSJG is currently being patented, the ingredients in YSJG cannot be published at this time.

For the control group, placebo granules are made from dextrin (95%) and *Herba pogostemonis* (5%) in order to achieve the same color, smell, taste, and texture as that of YSJG granules.

Both YSJG and placebo granules were manufactured by Beijing Tcmages Pharmaceutical Co. Ltd ([name]) according to the standards of Good Manufactoring Practice. Patients will be instructed to dissolve a sachet of granules (12.4 g) in 200 mL hot water and to take the solution orally twice a day for 12 weeks.

### Randomization and blinding

Block randomization was carried out in a 1:1 ratio according to the sequence generated with SAS (Version 7.0; Channel-leadian pharmaceuticals R&D, Co., Ltd; [name]). Drug codes, numbered from 1 to 84, and contained group assignments will be generated according to randomization numbers. Eligible patients will be randomized into the YSJG group or the placebo group by obtaining medicines associated with the given drug codes in accordance with the order of visits. Group assignments will not be revealed until the entire study is completed. Participants, investigators, statisticians, and all study staff are blinded.

### Outcome measures

#### Primary outcome measure

As pain is the most common complaint of AIMSS, we selected the Brief Pain Inventory-Short Form (BPI-SF) as the primary outcome measure to evaluate general pain. The BPI-SF, created by the Pain Research Group, is a 14-item questionnaire to measure both the intensity of pain as well as the interference of pain in the patient’s life on a scale ranging from 0 to 10.

#### Secondary outcome measures

##### Quality of life instruments

The Western Ontario and McMaster Universities Osteoarthritis Index (WOMAC) is a patient-reported outcome measure for assessing osteoarthritis of the knees or hips. It consists of 24 questions (5 pain, 2 stiffness, and 17 physical function) and can be completed in less than 5 minutes. We selected the WOMAC index to assess joint pain, stiffness, and functional status in the knees.

The Modified Score for the Assessment and Quantification of Chronic Rheumatoid Affections of the Hands (M-SACRAH) consists of three domains assessing pain, stiffness, and functional status in patients suffering from hand osteoarthritis and rheumatoid arthritis, answered on 100-mm visual analog scales. We selected the M-SACRAH to assess joint pain, stiffness, and functional status in the hands.

The Functional Assessment of Cancer Therapy-Breast (FACT-B), a quality of life instrument to assess the well-being of cancer patients, measures physical, social/family, emotional, and functional well-being as well as additional concerns commonly reported in breast cancer patients. The FACT-B scale has five response levels (ranging from ‘not at all’ to ‘very much’). Changes in the scores on these scales before and after intervention will be compared between the TCM group and the placebo group.

##### Bone mineral density

Musculoskeletal symptoms and bone loss are identified as the two main adverse effects of AIs. One study reported a correlation between AIMSS and osteoporosis (bone fractures)
[17]. In order to investigate the effects of YSJG on bone loss, bone mineral density (BMD) of the L2-L4 region of the spine and hip will be assessed before and after treatment (at weeks 0 and 12).

### Safety assessments

In order to assess the safety of YSJG, we will perform the following tests on all participants at the screening phase (week 0) and after treatment (week 12): blood routine test, urine routine test, feces routine test, kidney function test, liver function test, estradiol (E2), follicle-stimulating hormone, and serum levels of tumor markers (CEA, CA125, and CA153). In addition, investigators will ask every subject at each visit whether they have experienced any adverse events (AEs) during the study period. If there are any AEs, the investigator will provide appropriate treatment to the subject immediately and record AEs in a dedicated document in the case report form, including its severity and causality with the experimental agent. In the case of serious adverse events (SAEs), the investigator will offer appropriate treatment to the subject immediately and report the event to the Institutional Review Board within 24 hours from the time of recognition. If necessary, blinding will be broken by adequate procedure, and the documented procedure will be kept in the investigator study file.

### Sample size calculation

As there has been no similar TCM research on AIMSS to date, we calculated sample size according to another AIMSS study that used the same primary outcome measure (BPI-SF)
[18]. From the results of this previous study, the treatment group had a reduction of 1.5 points (the standard deviation was 2.1) on the mean BPI-SF worst pain compared with the control group. Therefore, 34 participants per group were deemed sufficient to achieve 90% power and a (one-sided) 5% significance level in detecting treatment differences. Considering a total withdrawal and dropout rate of 20%, we concluded that a total of 84 patients (42 per arm) would need to be recruited to ensure statistically significant results.

### Statistical analysis

Efficacy and safety analyses will be conducted according to the intention-to-treat principle. Missing values will be imputed by the last-observation-carried-forward method. All statistical analyses will be performed using Statistical Packages of Social Sciences software (SPSS 18.0, Channel-leadian pharmaceuticals R&D, Co., Ltd; [name]). Statistical significance will be defined as a one-sided *P*-value of <0.05. Demographic, clinical, and outcome variables will be described using means and standard deviations for continuous variables and percentages for categorical variables. The primary analysis will be to compare the mean pain scores from BPI-SF, the WOMAC, and the M-SACRAH and the mean joint stiffness and function scores from the WOMAC and the M-SACRAH between the TCM group and the placebo group. The secondary analysis will be to compare the mean scores from FACT-B and changes in BMD before and after treatment. Student’s t-tests and repeated-measure analyses of variance with a time-interaction term will be used to compare group differences.

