### Data collection and monitoring

This is a 24-week clinical trial, in which participants need to take research medication for 12 weeks, accept a 12-week follow-up, attend five assessment visits, obtain two sets of laboratory tests (safety assessments) and BMD analysis, fill in four sets of questionnaires at each visit, and stop taking other herbal medications (Table 
2).

**Table 2 T2:** Data collection schedule

	**Screening**	**Treatment**			**Follow-up**
Visit number	1	2	3	4	5
Week number	−2 to 0	4	8	12	24
Patient characteristics	✘				
Past history	✘				
AIMSS	✘				
ECOG	✘				
BPI-SF	✘	✘	✘	✘	✘
WOMAC	✘	✘	✘	✘	✘
M-SACRAH	✘	✘	✘	✘	✘
FACT-B	✘	✘	✘	✘	✘
Bone mineral density	✘			✘	
Safety assessment	✘			✘	
Combined medication	✘	✘	✘	✘	✘
Adverse events		✘	✘	✘	✘
Compliance		✘	✘	✘	

AIMSS, aromatase inhibitor-associated musculoskeletal symptoms; BPI-SF, Brief Pain Inventory-Short Form; ECOG, Eastern Cooperative Oncology Group; FACT-B, The Functional Assessment of Cancer Therapy-Breast; M-SACRAH, Modified Score for the Assessment and Quantification of Chronic Rheumatoid Affections of the Hands; WOMAC, Western Ontario and McMaster Universities Osteoarthritis Index.

Beijing Qihuang Medicine Clinical Research Center is responsible for quality control. Censors have regular visits (once a month) to monitor protocol violations, the recruitment rate, AEs and participant compliance.

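### Last observation carried forward, applied without exception, fixes the change in BMD and laboratory safety tests at zero for every patient without a week-12 value

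*Protocol article*

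**What the plan says.** In the Protocol article, Statistical analysis, two sentences stand next to each other, the first setting the scope and the second the rule for missing data: "Efficacy and safety analyses will be conducted according to the intention-to-treat principle. Missing values will be imputed by the last-observation-carried-forward method". The second sentence names no endpoint and makes no exception. The same section lists BMD change as a secondary analysis.

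The schedule is given elsewhere in the article:

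- **Laboratory tests (Safety assessments).** The blood, urine, feces, kidney and liver tests, estradiol, follicle-stimulating hormone and tumour markers are done "at the screening phase (week 0) and after treatment (week 12").
- **BMD (Bone mineral density).** Spine and hip "will be assessed before and after treatment (at weeks 0 and 12").
- **Data collection and monitoring.** Participants "obtain two sets of laboratory tests (safety assessments) and BMD analysis", and Table 2 marks both rows at screening and week 12 only.
- **Adverse events (Safety assessments).** These are handled differently: "investigators will ask every subject at each visit whether they have experienced any adverse events (AEs) during the study period". Table 2 has them at weeks 4, 8, 12 and 24.

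The Sample size calculation section allows for 20% total withdrawal and dropout. It does not say how much of this falls before week 12.

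**The concern.** On an outcome measured at several visits, LOCF carries forward the latest value on treatment. BMD and the laboratory panel have a single scheduled post-baseline measurement. If it is missing, the only earlier scheduled value is the pre-treatment one, so LOCF becomes baseline carried forward. A patient who was never re-tested enters the analysis as if she had been re-tested and found unchanged.

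For the laboratory panel, this means a new abnormality in such a patient cannot appear in the week-12 results. The panel is the only scheduled check of liver, kidney, hormone and tumour-marker values under a 12-herb product in women on aromatase inhibitors. For BMD, the imputed zeros enter a named secondary comparison. In both cases the imputed values make the data look complete, and a reader of the tables could not tell that they were not measured.

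**Working it through.** **Inputs.** 84 patients, 42 per arm; 20% total withdrawal and dropout (Sample size calculation). One baseline and one week-12 measurement (Safety assessments, Bone mineral density, Table 2). The share d without a week-12 value is not stated; I assume 0 to 20%. All rates, mean changes and dropout splits below are illustrative assumptions.

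**The plan's own figures.** With a difference of 1.5, SD 2.1, one-sided 5% and 90% power:

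n = 2 × (1.645 + 1.282)² × 2.1² / 1.5² = 33.6, so 34 per group, as stated.

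34 / 0.8 = 42.5 per arm, or 68 / 0.8 = 85 in total, against the stated 84. The small gap is rounding and does not matter here.

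**Step 1: patients affected.** Number with an imputed zero = 84 × d.

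| d | Patients with imputed zero | Recorded mean change, as share of measured patients' mean |
|---|---|---|
| 5% | 4.2 | 95% |
| 10% | 8.4 | 90% |
| 15% | 12.6 | 85% |
| 20% | 16.8 | 80% |

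The last column is (1 − d) × m + d × 0 = (1 − d) × m, where m is the mean change in patients who have both measurements.

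**Step 2: new laboratory abnormalities at d = 20%.**

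- True rate 10% in everyone: recorded 0.8 × 10% = 8%.
- True rate 10% in measured patients and 30% in those missing: true overall 0.8 × 10% + 0.2 × 30% = 14%; recorded still 8%.
- True rate 10% in measured patients and 0% in those missing: true overall 8%, recorded 8%, so no understatement.

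**Step 3: difference between arms.** Recorded difference = (1 − dT) × mT − (1 − dC) × mC, with T for YSJG and C for placebo. For the comparison with the truth, missing patients are assumed to change as much as the measured patients in their arm.

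| dT / dC | mT, mC | True difference | Recorded difference |
|---|---|---|---|
| 20% / 20% | −0.5, −1 | +0.5 | +0.40 |
| 30% / 10% | −1, −1 | 0 | +0.20 |
| 10% / 30% | −1, −1 | 0 | −0.20 |
| 30% / 10% | −0.5, −1 | +0.5 | +0.55 |
| 10% / 30% | −0.5, −1 | +0.5 | +0.25 |

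Equal dropout shrinks the difference by the factor (1 − d). Unequal dropout can create a difference where none exists, in favour of either arm, and can enlarge or reduce a real one.

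**The case against.** Several stronger readings are tempting, and the document does not support them.

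- **That every dropout is recorded as no change.** Follow-up runs to week 24. A patient lost after week 12 already has both measurements. Because the 20% is a total, 17 of 84 and a 20% shrinkage are upper figures at the planned dropout.
- **That harm or bone loss is always understated.** Shrinkage is certain only relative to the measured patients' mean. Against the truth it depends on how the missing patients really changed, and under unequal dropout the comparison can move either way. A real BMD benefit of YSJG would be diluted under equal dropout just as a loss would.
- **That a patient who stops for toxicity becomes invisible.** Adverse events are recorded at each visit with severity and causality, and LOCF on a laboratory value does not erase them. Nor does the rule make her tests normal: it repeats her baseline, whatever that was. The article also plans the week-12 tests for all participants, so stopping the granules need not mean missing them.
- **That power is clearly lost.** With an assumed 0.70 SD shift in the active arm, 42 per arm and a two-sided 5% test, power at equal 20% dropout is about 79% with LOCF and 80% on observed data, because the variance shrinks too. At 30%/10% (YSJG/placebo) it is about 67% against 80%; at 10%/30%, about 89% against 80%. Neither the shift nor the splits come from the article, so no loss of power can be claimed.

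It may also be said that a fuller plan could exempt these endpoints. That is possible. But the article does state a rule, and that rule combined with the stated schedule gives the result shown. This is not a detail left open.

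**Conclusion.** The point stands in limited form. As written, LOCF covers BMD and the laboratory safety tests, and for patients without a week-12 value it enters a change of zero that nobody measured. Relative to the measured patients, each arm's mean change is reduced by up to 20%, with up to about 17 of 84 values imputed, if all of the planned dropout occurs before week 12; less if part of it occurs later. The arm difference is attenuated under equal dropout and biased in an unpredictable direction under unequal dropout.

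The mechanism follows directly from the text. The size rests on the assumed d, and the direction against the truth rests on unobserved changes in those who leave. The BPI-SF pain outcome and the adverse-event record are outside this point. It is worth correcting because it concerns the safety panel and a secondary endpoint and the correction is cheap, but it does not threaten the trial's main comparison.

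**What to change.** 1. State that LOCF does not apply to the laboratory safety tests or to BMD.
2. Report laboratory safety on observed post-baseline values, with the number missing in each arm.
3. Analyse BMD change on observed week-12 data adjusted for baseline, with multiple imputation as a sensitivity analysis.
4. State that the week-12 tests already planned for all participants are also sought from those who stop the granules early.

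Items 1 to 3 are changes of wording and analysis. Item 4 uses tests already in the schedule, but needs some effort to bring these patients back. Observed data do not remove bias if those who leave differ: in the 14% example above they would show 10%. They do avoid invented values and leave the gap in view. The cost is visible missing counts and slightly smaller analysed numbers for these endpoints.

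### Safety is placed under intention to treat along with efficacy, so patients who took no granules, or the other product, count in the assigned arm; the effect is very small and may be zero

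*Protocol article*

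**What the plan says.** The Statistical analysis section covers both efficacy and safety in one sentence: "Efficacy and safety analyses will be conducted according to the intention-to-treat principle". No other section defines a separate safety population. Safety assessments lists the laboratory tests and says how adverse events are asked about and recorded, but not who is counted.

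Four other places bear on the point:

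- Background gives safety as a purpose of the trial: it is needed "to investigate the efficacy and safety of YSJG on AIMSS".
- Study design puts allocation after a run-in: "After a 2-week run-in period, eligible participants will be randomly assigned to the TCM group or the placebo group". All participants take an aromatase inhibitor and are prescribed calcium with vitamin D.
- Randomization and blinding makes allocation and dispensing one step. Patients are randomised "by obtaining medicines associated with the given drug codes in accordance with the order of visits".
- Data collection and monitoring provides monthly visits "to monitor protocol violations, the recruitment rate, AEs and participant compliance". In Table 2, compliance is first recorded at week 4.

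**The concern.** Intention to treat suits the efficacy comparison because it preserves the randomised groups and does not flatter the treatment. The usual safety question is different: what happened to patients who took each product. Counting everyone as randomised answers it imperfectly in two ways.

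- A patient who collected her sachets and took none contributes no exposure but stays in the denominator. Her chance of an event is the background chance, so she moves her arm's rate toward that level.
- A patient who received the other product has her events attributed to the one she was assigned.

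If YSJG causes more events than placebo, both mainly make it look closer to placebo, which is the less cautious direction for a safety assessment. The article states this population outright, so it is not a detail merely left to an analysis plan.

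**Working it through.** **Inputs from the article.** The denominator is 42 per arm: "a total of 84 patients (42 per arm) would need to be recruited". It can be reproduced from Sample size calculation (difference 1.5, SD 2.1, one-sided 5%, 90% power): 2 × (1.645 + 1.282)² × (2.1/1.5)² = 33.6, so 34 per group, as stated. Then 34/0.8 = 42.5, against 42 stated. The rounding does not matter here.

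**Inputs assumed.** The article gives no adverse-event rates and no number of never-dosed or wrongly supplied patients. Assumed here: true rates of 20% on YSJG and 10% on placebo; a 10% background rate in a never-dosed patient; 0 or 1 affected patient per arm.

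**Reference.** With everyone dosed as assigned, the difference is 10.0 points and the risk ratio 2.00. The standard error of the difference is √[(0.20 × 0.80 + 0.10 × 0.90)/42] = √(0.25/42) = 0.0772, or 7.7 points.

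**Never-dosed patient at the background rate.**

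- One in the YSJG arm: (41 × 0.20 + 0.10)/42 = 19.76%, against 10%. Difference 9.8 points, risk ratio 1.98.
- One in the placebo arm: (41 × 0.10 + 0.10)/42 = 10%. Nothing changes.
- One in each arm: 19.76% against 10%. Difference 9.8 points, risk ratio 1.98.

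**Never-dosed patient with no events at all (limiting case).**

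- One in the YSJG arm: 41 × 0.20/42 = 19.52%. Difference 9.5 points, risk ratio 1.95. This is the upper bound on shrinkage from one never-dosed patient.
- One in the placebo arm: 41 × 0.10/42 = 9.76%. Difference 10.2 points, risk ratio 2.05.
- One in each arm: 19.52% against 9.76%. Difference 9.8 points, risk ratio 2.00.

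**Patient on the other product.**

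- One in either arm: difference 9.8 points (risk ratio 1.98 if in the YSJG arm, 1.95 if in the placebo arm).
- One each way: (41 × 0.20 + 0.10)/42 = 19.76%, against (41 × 0.10 + 0.20)/42 = 10.24%. Difference 10.0 × 40/42 = 9.5 points, risk ratio 1.93.

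**Scale.** The shifts are 0.24 or 0.48 points. Divided by 7.72, they are 3.1% and 6.2% of one standard error.

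**Range.** With k never-dosed patients in the YSJG arm at the background rate, the difference is 10.0 × (42 − k)/42: 9.5 points for k = 2 and 9.0 for k = 4. With rates of 30% and 10%, one swap each way gives 20.0 × 40/42 = 19.0 points. With k = 0 and no swaps, nothing changes.

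**The case against.** The strongest objection is that nothing turns on this. Allocation is the hand-over of the coded pack after a run-in, so a never-dosed patient must collect the granules and take none. A wrong-product case needs a number issued out of order, a packaging error or a resupply error, and monthly monitoring looks for violations. The 20% allowance in the sample size is for withdrawal and dropout, not for never starting. The article names no adverse-event hypothesis that would depend on the rule. All of this stands, and it limits the severity.

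A second objection is that comparing events as randomised is a coherent choice, and that investigators record causality for each event, so individual attribution is not lost. That is fair, and is a reason to keep an as-randomised table as support. It does not change the denominator or the arm in which an event is counted.

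A third is that the remedy reaches few patients. Someone who leaves before week 4 may have no compliance record, and presuming her dosed keeps her in. This also stands: only documented never-dosed patients are removed.

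A reader might infer more than the documents support: that a never-dosed patient always lowers her arm's rate, that one in the placebo arm widens the difference, or that equal numbers in both arms leave the risk ratio unchanged. The last two hold only if the never-dosed patients are event-free, and the first only if their risk is below the arm's own rate. These participants all take an aromatase inhibitor with calcium and vitamin D and are asked about adverse events at each visit, so background events are to be expected.

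**Conclusion.** The point holds as a minor one. The article fixes a safety population that does not quite match the question of what happens to patients who take YSJG. If YSJG has the higher true rate, the main consequence is a slightly reduced difference. A never-dosed patient in the placebo arm has little or no effect unless she is event-free.

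Under the assumed 20%, 10% and 10% rates, and at most one affected patient per arm, the difference falls from 10.0 to between 9.8 and 9.5 points, well inside sampling error. The event rates and patient counts are assumptions, and zero affected patients is possible. A reader might infer that the rule could hide a real harm; the documents give no ground for that, and no safety conclusion is likely to depend on it. The sample size, significance level and primary efficacy result are unaffected.

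**What to change.** Limit the intention-to-treat sentence to efficacy, and add wording such as: *Safety analyses include all patients who took at least one dose of granules, grouped by the product actually received. Patients whose dosing status is unknown are presumed dosed. The number in each arm with no post-dose safety assessment is reported.* An as-randomised safety table may be kept as supportive. The change should be made before unblinding.

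The cost is a few lines of text and no new data collection. Safety and efficacy denominators may differ slightly. Because early leavers with unknown dosing are kept, the change may in practice alter nothing.
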